**Fig. 1 Fig1:**
[figure not shown]
ED workflow and procedures for intervention participants. ED, emergency department; EKG, electrocardiogram; PT, physical therapy

### Follow-up procedures

All participants receive telephone calls every 2 weeks to prompt them to complete fall calendars and provide them an opportunity to ask questions about study procedures (Fig. 2). At 30 and 90 days after enrollment, participants complete a follow-up survey over the telephone, via e-mail, or in person, depending on participant preference. At 180 days after enrollment, research staff, who are blinded to arm assignment, conduct a home visit with participants to perform the final procedures and assessments (Table 2). Fall calendars are collected at the conclusion of the visit. Research staff masked to arm allocation also abstract study outcomes from the EHR to confirm and supplement the data recorded in the fall calendars.

**Fig. 2 Fig2:**
[figure not shown]
Schedule of enrollment, interventions, and assessments. PCP, primary care provider; TUG, Timed Up and Go test; Barthel ADL, Barthel Index for Activities of Daily Living; MRAP, medication-related action plan; SNF, skilled nursing facility

**Table 2 Tab2:** Study instruments and timeline of assessments

Instrument	Description	Administration
Process evaluation		
Screening, eligibility, and retention	• Records how many patients were screened, agreed to participate, were recruited, received intended treatment, and were retained	• Baseline, 180 days
ED component and fidelity	• Records index visit ED LOS, time between consult call and arrival of pharmacist and PT, length of each consult, accuracy and completeness of action plan compared to the protocol	• Baseline
Patient, caregiver, and clinician feedback	• Tracks satisfaction with each component of the evaluation, perceived barriers and facilitators, and collects suggestions for improvement of the intervention	• Baseline
Follow-up component	• Tracks follow-up phone and in-person sessions with the research staff, PT, and any home services. Records uptake of recommendations made on the action plan for intervention participants	• 30, 90, 180 days
Outcome evaluation—feasibility, fidelity, and initial efficacy		
Enrollment questionnaire	• Demographic characteristics (includes marital status, whether the patient lives alone or with others, educational attainment, current employment.) • Prior fall history, comorbidities, ED index visit fall circumstances, and injuries	• Baseline • < 5 min
Six-Item Screener (SIS) [19]	• 6-point questionnaire to measure cognitive impairment for study screening [19], < 4 indicates high risk for cognitive impairment	• Baseline • 2 min
Timed Up and Go (TUG) test [21]	• Timed test of how long it takes the patient to get up from a chair, walk 10 feet, and return to the chair • Validated measure of current function, balance, and fall risk • A TUG > 12 seconds identifies those patients at greater risk for subsequent falls	• Baseline, 180 days • < 5 min
Barthel Index for Activities of Daily Living (ADL) [22]	• Used to assess functional independence [22] • Information can be gained by self-report or caregiver report	• Baseline, 30, 90, 180 days
Tinetti [23]	• Validated measure of gait and balance • Predicts falls	• Baseline • < 5 min
5 Times Sit to Stand [24]	• A measure of functional lower limb muscle strength	• Baseline
AM-PAC “6-clicks”	• Test of activity limitations and function [25] used to help determine need and intensity of outpatient services such as PT, safety of discharge, and to predict falls and healthcare utilization	• Baseline • 1 min
Falls Efficacy Scale-International [26]	• Measures fear of falling, which increases fall risk	• 180 days
Medication questionnaire	• Records all current and new prescriptions, over-the-counter and herbal medication, recommendations made by the pharmacist, recommendations accepted by the patient, and date of initiation/cessation	• Baseline, 180 days • 25 min
Outcome instrument	• Records follow-up falls and injuries by self-report and EHR review • Records subsequent ED visits and hospitalizations	• 30, 90, 180 days • 5 min

*ED* emergency department, *LOS* length of stay, *SIS* Six-Item Screener, *TUG* Timed Up and Go, *ADL* Activities of Daily Living, *PT* physical therapy, *AM-PAC* Activity Measure for Post-Acute Care, *EHR* electronic health record

### Efforts to improve recruitment and retention

A number of steps are taken to enhance recruitment and retention of participants. First, an Epic® Best Practice Advisory alerts research staff that a potentially eligible study subject is in the ED. Second, patients are asked during their index visit how they prefer to be contacted (by telephone or e-mail) and their preferred time of day for follow-up communication. Research staff schedule future follow-up telephone calls with patients during the 2-week reminder calls. If patients cannot be reached by telephone by the research staff, the principal investigator (PI) will attempt to contact them. Finally, an in-person visit is conducted for participants who cannot be contacted.

### Data collection

All participants receive an in-ED assessment by the research staff and scheduled follow-ups at 30, 90, and 180 days. Caregiver and clinician interviews occur only during the index ED visit. The information that is collected from participants and the EHR is summarized in Table 2.

We ensure fidelity to the research protocol through several means. First, the study coordinator reviews baseline enrollment data on a weekly basis. Second, the study team reviews on a monthly basis the proportion of subjects who are eligible, approached, consent to participate, and enrolled. Reasons for refusal are tracked to allow the study team to modify how they communicate study details when they approach the participant and for subsequent study planning. The PI holds weekly meetings with the research staff to discuss study progress and address concerns. Finally, the biostatistician performs automated and manual checks in the REDcap data collection program to ensure data quality.

### Sample size

This early stage investigation is designed to provide a preliminary indication of the proportion of screened participants who are eligible, recruited, and retained, with the goal of estimating these proportions with a standard error of less than 5%. Assuming the maximum possible variability for each of these proportions, the sample size of 120 produces a standard error of 4.6%, enabling estimation of a margin of error of ± 8.9%. A second feasibility aim was estimating if there was a major difference in ED LOS between groups. For *α* = 0.05 with a two-sided test and assuming a standard deviation of 120 min, a sample size of 52 per group has adequate power (*β* = 0.83) to detect a difference of 65 min. or more. To allow for non-parametric tests which may be necessary given the skewed nature of ED visits, a 15% increase in sample size or 60 per group will yield the same power [27].

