**Methods:**

GAPcare is a randomized single-blinded pilot study. Participants in GAPcare are 120 older adults (≥ 65 years old) who present to 1 of 2 academic US EDs after a fall. We randomly assign participants 1:1 to an intervention or a usual care (control) arm. In the intervention arm, the patient’s ED physician, a pharmacist, and a physical therapist (PT) collaborate to identify and address any risk factors that may have contributed to the fall. Intervention arm participants and their caregivers return home with a medication-related action plan to taper or stop potentially inappropriate medications and to address polypharmacy and a PT assessment and plan. Participants in the usual care arm receive standard assessments and care in the ED and a home safety brochure. Participants in both study arms complete fall calendars for 6 months to document the number of falls and healthcare visits during follow-up. The primary outcome is feasibility of the GAPcare fall prevention intervention (number and proportion of screened participants who are eligible, recruited, and retained; impact on ED length of stay), while the secondary outcome is to estimate its initial efficacy.

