#### Fidelity

We will use descriptive statistics to assess key parameters of fidelity: receipt of the pharmacy and PT consultations, MRAP provision to patients and receipt of the MRAP by PCPs, fall calendar completion, and uptake of recommendations by patients and PCPs at 6-month follow-up. Implementation activities will be measured against recommendations and categorized into three level of adherence: adherent, partially adherent, and non-adherent.

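### The 4.6% standard error and ±8.9% margin use the 120 randomised participants as denominator; they fit retention but are too wide for eligibility and recruitment

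*Protocol article*

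**What the plan says.** In the protocol article, the Sample size section says the study will give a "preliminary indication of the proportion of screened participants who are eligible, recruited, and retained". The precision target follows: "with the goal of estimating these proportions with a standard error of less than 5"%. The worst case is taken for all three together ("Assuming the maximum possible variability for each of these proportions"), and the result is that "the sample size of 120 produces a standard error of 4.6"%, "enabling estimation of a margin of error of" ±8.9%.

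The Methods paragraph of the Abstract words the primary outcome in the same way: "number and proportion of screened participants who are eligible, recruited, and retained". It also says who the 120 are: "Participants in GAPcare are 120 older adults", who are then randomised 1:1. The Recruitment and enrollment section puts randomisation after record review, confirmation of eligibility and written consent. The Feasibility section lists the number screened, the proportion eligible and the number recruited as separate quantities. The article gives no expected number screened or eligible.

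**The concern.** A standard error needs the denominator of the proportion it describes. The article names screened patients as the denominator and then computes on the randomised participants, who are what remains after screening, eligibility checks and consent. One figure is thus attached to three proportions, although at least two of them rest on a different and larger group.

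Feasibility is the primary outcome, and this paragraph gives the precision claimed for it. The pilot is meant to inform a definitive trial, for which eligibility and recruitment rates are key planning inputs. A reader planning that trial is given a precision for those rates that does not apply, and no planned denominator from which to work out the right one. An analyst who took the paragraph literally could also compute intervals on 120 for proportions that do not have 120 in the denominator.

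**Working it through.** **Inputs.** n = 120, target SE below 5%, maximum variability (p = 0.5), stated SE 4.6% and margin ±8.9%: all from Sample size. The 120 are participants randomised 1:1: Abstract, Methods. Randomisation follows eligibility and consent: Recruitment and enrollment. The number screened, N, is not given, so a range is assumed below.

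**Step 1: reproduce the stated figures.** For a single proportion, SE = √(p(1−p)/n).

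- √(0.25/120) = 4.56%, stated as 4.6%.
- 1.96 × 4.56% = 8.95% (8.946% unrounded), stated as 8.9%. The article gives no confidence level; 95% reproduces the figure.

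The arithmetic is right, and it shows that 120 was the denominator used.

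**Step 2: recruited out of screened.** With 120 recruited from N screened, p = 120/N and

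SE² = p(1−p)/N = 120(N−120)/N³.

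Setting the derivative to zero gives N = 3(N−120), so N = 180 and p = 2/3. There SE = √(120 × 60/180³) = 3.51%, and 1.96 × 3.51% = 6.9%. This is the largest value that recruitment out of screened can take. Treating enrolment as continuing until 120 are recruited gives the same expression, p√((1−p)/120), which at p = 2/3 is again 3.51%.

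If recruitment is meant out of eligible patients, the same algebra applies with the number eligible in place of N, and the ceiling is the same.

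**Step 3: eligible out of screened.** Let E be the number eligible, with E ≥ 120. For fixed E the SE is largest at N = 1.5E, where SE = √(0.5/(3.375E)) = √(0.148/E). This is largest at the smallest permitted E, and √(0.148/120) = 3.51%. The ceiling is therefore also 3.5% (±6.9%).

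**Step 4: why 4.6% cannot arise for these two.** It would need p = 0.5 on a denominator of 120, which means 60 eligible or 60 recruited. That contradicts an enrolment of 120. For recruitment, p = 0.5 requires N = 240, and the SE is then √(0.25/240) = 3.2%.

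**Step 5: illustrative range for N (assumed, not in the article).**

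| Screened | SE at p = 0.5 (95% margin) | Recruited proportion, 120/N | Its SE (95% margin) |
|---|---|---|---|
| 240 | 3.2% (±6.3%) | 0.50 | 3.2% (±6.3%) |
| 400 | 2.5% (±4.9%) | 0.30 | 2.3% (±4.5%) |
| 600 | 2.0% (±4.0%) | 0.20 | 1.6% (±3.2%) |
| 1200 | 1.4% (±2.8%) | 0.10 | 0.9% (±1.7%) |

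**Step 6: is the goal still met?** At p = 0.5 an SE of 5% needs a denominator of 0.25/0.05² = 100. Every denominator here is at least 120, so the goal holds for all three proportions.

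**The case against.** The strongest reply is that nothing has been miscalculated and nothing goes wrong. The section states a worst case. The 120 randomised are the smallest group on which any of the three pooled proportions could be taken, so sizing on them secures the 5% goal for all three. The ±8.9% is a planning figure; nothing in the article says it will be attached to a result. The same section also reaches 60 per group from a comparison of ED length of stay, so this paragraph is not the only support for 120.

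All of that stands, and it limits the point to the description of precision. It does not remove it. The article does not present 4.6% as a bound taken from the smallest group; it assigns it to the proportions of screened patients, two of which cannot reach it.

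Two details of denominator are also open. Taking recruitment out of eligible patients is a reading; the article names only screened patients. And retention too is worded as a proportion of screened patients. On that literal reading 4.6% would again be only an upper bound, reached if nobody screened failed to enrol. Retention among those randomised is the reading under which the figure is exact.

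A reader might go further and infer that the figures are too narrow by arm, since √(0.25/60) = 6.5% (±12.7%) misses the 5% goal. The article does not support that as an error. Its goal covers only the eligible, recruited and retained proportions, and it promises no precision by arm. The Fidelity section lists items such as "receipt of the pharmacy and PT consultations" for descriptive reporting, with no precision target, and one of them, fall calendar completion, applies to both arms.

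**Conclusion.** The point holds as a mismatch between the proportions named and the denominator used. The figures 4.6% and ±8.9% are the exact worst case for pooled retention among the 120 randomised. For eligibility and recruitment they are too wide: the standard error is at most about 3.5% (±6.9%), and past 180 screened this ceiling falls.

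The ceiling rests on two assumptions: that the planned 120 are enrolled, and that everyone enrolled was screened and eligible first, as the article describes. The values for particular numbers screened are illustrative.

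The error is conservative. It is no ground for saying that the 5% goal is missed, that the arithmetic is wrong or that 120 is too few.

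**What to change.** Reword the precision paragraph in Sample size:

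- Limit 4.6% and ±8.9% to pooled retention among the 120 randomised, and state that the margin is at 95% confidence if that is what was meant.
- Name the denominator of each other proportion: screened patients for eligibility; screened patients, or eligible patients if that is intended, for recruitment.
- Give an expected number screened, or a plausible range, and state the precision of eligibility and recruitment from it. Report each confidence interval on its own denominator.
- Align the wording of the primary outcome in the Abstract, so that retention is not described as a proportion of screened patients unless that is meant.

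The cost is a few sentences and one planning figure for the number screened. The sample size and the planned analyses do not change, and the Feasibility section already provides for collecting the counts needed.

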### Recruitment and enrollment

Research staff review the ED Electronic Health Record (EHR) (Epic®) for ED patients presenting after a fall. Participants are recruited when PT and pharmacy specialists are available, Monday through Friday from 7 AM to 4 PM. The patient’s ED clinician is asked to confirm that he/she plans to discharge the patient home. If this outcome is likely, the research staff confirms eligibility with the patient, invites the patient to enroll, and asks them to provide written consent for participation. Caregivers and treating clinicians are also asked to consent to study participation.

We first assess each patient’s decisional capacity. For patients who score less than 4 on the Six-Item Screener [19] (a screen for cognitive impairment) but are interested in participating in the study, the legally authorized representative is asked to provide written consent.

After consent, each participant is randomized 1:1 to the intervention arm or usual care. Randomization is performed using REDcap and is based on randomization tables that stratify patients by study site. Enrollment staff do not have access to the allocation scheme before enrolling participants. It is not possible to blind the participants and treating clinicians to the allocation arm as they would be able to identify pharmacists and PTs at the bedside. However, the staff member who performs the assessment at 6-month follow-up is blinded to allocation arm.

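### The stated power of 0.83 to detect a 65-minute difference in ED length of stay does not follow from its inputs: 52 per group gives 0.78, and 60 per group after the plan's own rank-test allowance gives 0.78 again.

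*Protocol article*

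**What the plan says.** The Sample size section of the protocol article justifies the sample size in two ways. The first is the precision of the feasibility proportions. The second is a power calculation for the difference in ED length of stay (LOS) between arms.

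The power calculation takes a two-sided α of "0.05 with a two-sided test and assuming a standard deviation of 120 min". It states that "a sample size of 52 per group has adequate power", gives the value as β = 0.83, and sets the target as "to detect a difference of 65 min. or more". Because LOS is skewed and non-parametric tests may be needed, it then says that "a 15% increase in sample size or 60 per group will yield the same power".

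Three other places bear on this. The abstract's Methods paragraph sets the total ("Participants in GAPcare are 120 older adults") and lists the effect on ED LOS within the primary outcome. Recruitment and enrollment fixes equal allocation ("each participant is randomized 1:1 to the intervention arm or usual care"). The Feasibility paragraph under Data analysis names the Wilcoxon-Mann-Whitney test for LOS, with a bootstrap confidence interval for the median difference, so the rank-test allowance applies to the planned analysis.

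**The concern.** The section supplies every input to a standard two-sample calculation, and the stated power does not follow from them. The second sentence carries the error forward. It says that 60 per group with a rank test has the same power as 52 per group with a t-test, so if the value at 52 is wrong, the value at 60 is wrong by the same amount.

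The symbol is also wrong. β conventionally denotes the type II error, so β = 0.83 read literally is an 83% chance of missing the difference. The surrounding words show that power was meant.

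This is the only power figure in the article, and the limitations paragraph of the Discussion disclaims power for falls. The pilot asks whether the intervention fits within an ED visit, so a non-significant LOS comparison may be read as evidence that visits are not prolonged. How far such a result reassures depends on the chance of missing a 65-minute increase, and the text understates that chance.

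**Working it through.** **Inputs** (all from the Sample size section, except allocation, which is from Recruitment and enrollment): two-sided α = 0.05; SD σ = 120 min; difference δ = 65 min; n = 52 per group, 1:1; rank-test allowance 15%, final n = 60 per group; stated power 0.83.

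**1. Power at 52 per group.**
- Standardised difference: δ/σ = 65/120 = 0.5417.
- Noncentrality: (δ/σ)·√(n/2) = 0.5417 × √26 = 2.762.
- Normal approximation: Φ(2.762 − 1.960) = Φ(0.802) = **0.789**.
- Two-sample t-test (noncentral t, 102 df): **0.781**.

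The stated 0.83 is not reproduced; the gap is 4 to 5 percentage points. A one-sided test does not explain it either, since it gives 0.864 (t) or 0.868 (normal).

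**2. What would give 0.83.**

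| n per group | Power, two-sided t-test |
|---|---|
| 52 | 0.781 |
| 55 | 0.804 |
| 58 | 0.824 |
| 59 | 0.831 |
| 60 | 0.837 |

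By t-test, 0.83 needs 59 per group; by the normal approximation it needs 58. Adding the 15% allowance would bring these to about 67 or 68 per group (58 × 1.15 = 66.7; 59 × 1.15 = 67.9). With n held at 52, a power of 0.83 would need an SD of about 113 min (t) or 114 min (normal) instead of 120.

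The stated value is close to the t-test power at the final 59 to 60 per group. A plausible origin is that power at the inflated size was attached to the size before inflation, but the document does not show this.

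**3. The step to 60 per group.** 52 × 1.15 = 59.8, which rounds to 60, so this step is correct. Undoing the allowance gives 60/1.15 = 52.2 effective per group, with power **0.782** (t) or 0.790 (normal). The two sizes do have the same power, but it is 0.78 to 0.79, not 0.83.

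**4. How much depends on the allowance.** The 15% rule is close to the lower bound for the efficiency of the Wilcoxon test relative to the t-test, which is 0.864.
- At the bound: 60 × 0.864 = 51.8 effective per group, power 0.780.
- With normal data (efficiency 0.955): 60 × 0.955 = 57.3 effective per group, power 0.820. A simulation of the Wilcoxon-Mann-Whitney test with normal data gave 0.818.
- With an assumed lognormal LOS (mean 300 min, SD 120 min) and a pure 65-minute shift, simulation gave 0.90. The mean of 300 min is an assumption; the document gives none.

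**5. Detectable difference at 52 effective per group** (t-test, SD 120 min): 80% power at 66.6 min and 83% power at 69.2 min.

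**6. Type II error.** 1 − 0.781 = 0.219, against the implied 1 − 0.83 = 0.17. The ratio is 0.219/0.17 = 1.29, so the error is about 30% larger than stated.

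**The case against.** The arithmetic at 52 per group is not in dispute. The best reply concerns the trial as it will be run, with 60 per group and a rank test. There, 0.78 is close to a worst case. With normal data the power is about 0.82, nearly the stated value, and under an additive shift of a skewed distribution it can be about 0.90. It can also be lower: with a multiplicative effect on lognormal LOS and the same mean difference, it was about 0.77. The document gives no LOS distribution, so it cannot be said that the trial will necessarily fall short of 0.83, or of 0.80. That limit stands.

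The practical weight is also modest. This is a pilot, and LOS is introduced as the second feasibility aim. The precision target that comes first in the section does reproduce: √(0.25/120) = 4.6%. The LOS result will be reported with a confidence interval, and the article ties no progression rule to its significance. On the plan's inputs, 80% power is reached at 66.6 min rather than 65 min, a change of 1.6 min against an SD of 120 min. The β symbol is an editorial slip that few readers would take literally.

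None of this repairs the text. The claim about 52 per group is false on its own inputs. The claim about 60 per group is defined as equal to it through the 15% rule, so a more favourable assumption about rank-test efficiency would be a different argument from the one the plan makes.

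**Conclusion.** The point holds. With SD 120 min, a 65-minute difference, two-sided α of 0.05 and 52 per group, power is 0.78 by t-test (0.79 by normal approximation), not 0.83. Under the plan's own 15% allowance, 60 per group gives the same 0.78, just below the customary 0.80 that the word adequate usually implies.

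The result at 52 per group rests only on the stated inputs. The result at 60 per group rests also on the 15% rule; with normal LOS it would be about 0.82. This is an error in a stated figure for a component of the primary outcome, small in practical effect, and it does not put the sample size of 120 in doubt.

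**What to change.** Keep 120 participants and restate the calculation, for example:

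> For two-sided α = 0.05 and a standard deviation of 120 min, 52 per group gives power (1 − β) of 0.78 to detect a difference of 65 min; 80% power corresponds to about 67 min and 83% to about 69 min. Enrolling 60 per group, a 15% increase, preserves this power for a rank test at close to its lowest efficiency relative to the t-test; with normally distributed data the power would be about 0.82.

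Write power, or 1 − β, wherever the text now gives β. If 0.83 is to be kept as the headline figure, the sentence must instead name the size, difference or SD that produces it.

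The cost is a sentence or two and a slightly less favourable figure. No participants are added, and neither the design nor the analysis changes.
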